### Control group

Both intervention and control group participants will receive services from the community centers as usual. The community centers will provide regular onsite educational sessions and workshops for enhancing the caregiving knowledge of caregivers. Attendance at these lectures is not mandatory, and all subjects are welcomed to join.

### Data collection

Data will be collected at two time points – pre-intervention (T1) and post-intervention (T2). The data will be collected through phone call by a trained RA. Five percent of completed questionnaires (i.e., 4) will be randomly selected for an independent review to ensure the quality of the collected data.

## Outcome measures

### Primary outcome

The primary outcome of the study is the stress level of the caregivers. Stress levels will be measured using the 14-item Chinese version of the Perceived Stress Scale (PSS) (20). It has been applied extensively to measure the degree of perceived stress of informal caregivers. The total score ranges between 0 (minimum stress perceived) and 56 (maximum stress perceived), with higher scores representing greater perceived stress levels. The Chinese version was shown to have good validity and reliability. The Cronbach’s alphas of the total scale and the subscales were 0.881, and 0.793, 0.892 (21).

### Secondary outcomes

The secondary outcomes include self-efficacy, depression levels, quality of life, and caregiving burden.

*Self-efficacy* – The General Self-Efficacy Scale (CGSE) will be used to assess the self-perceived ability to cope with stressful life events (22). The Chinese version of CGSE contains 10 items and is scored on a 4-point Likert scale ranging from 1 (not at all true) to 4 (exactly true). The total score ranges from 10 to 40, with higher scores indicating a greater belief in one’s competence to deal with the difficulties. High internal consistencies were found, with a Cronbach’s alpha of 0.91.

*Depression* – Depression levels will be measured using the Chinese version of The Center for Epidemiologic Studies Depression Scale (CES-D). The CES-D is a self-reported scale that is used to measure the presence of depressive symptoms (23). This 4-point scale is a 20-item instrument. Total scores range from 0 to 60, with higher scores indicating more depressive symptoms. The scale was found to have a sensitivity and specificity of 100 and 76%, respectively, for a cut-off score of 16. The Cronbach’s alpha coefficient was 0.86.

*Quality of life* – The Chinese (HK) version (SF-12v2-HK) of the 12-item Short Form Health Survey version 2 will be used to assess the quality of life of the informal caregivers. The questionnaire contains 12 items involving different domains of health concepts, which include physical functioning, role limitations due to emotional problems, role limitations due to physical problems, a mental health scale, general health, bodily pain, and social functioning and vitality (energy/fatigue) (24). The internal consistency (Cronbach’s alpha) of this scale is >0.7 and its test–retest reliability estimates (ICC) is >0.7.

*Caregiving burden*– Caregiving burden will be measured using the Zarit Burden Interview (ZBI) (25). It contains 22 items and is scored on a 5-point Likert scale ranging from 0 (never) to 4 (nearly always). The total score ranges from 0 to 88, with a score of 24 or above possibly indicating a higher chance of developing depression. The sensitivity and specificity of the ZBI were 85.2 and 74.8%, respectively, for a cut-off point of 34. The measure has been widely used in studies focusing on informal caregivers, and the Chinese version of the ZBI is highly reliable and valid (26).

### Background demographic data

The background demographic data of the participants will be collected at baseline (T1). The data will include age, gender, marital status, level of education, number of caregiving hours per week, work status, duration of caregiving, financial situation, family structure, person with whom they live, and experience of using a smartphone. See Figure 3.

**Figure 3 fig3:**
[figure not shown]
Schedule of enrollment, interventions, and assessments.

### Ethical considerations

Ethical approval was obtained from the Ethics Sub-committee of the study university. The RA will convey information about the program, including its potential benefits, risks, and the issue of confidentiality during subject recruitment. Each participant who agrees to participate in the program will be required to sign a consent form upon enrollment. The collected data will be accessed solely by the research assistants and no personal information will be disclosed. Such data will include the demographic data of the subjects, the outcome measures, and the user ID and password for accessing the virtual discussion forum. All data will be stored in a password-protected database.

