### Study design and setting

This is a single-blinded, two-armed, randomized controlled trial, where the research assistant who is responsible for data collection is blinded but the provider is not blinded. This study is supported by two community centers of a non-governmental organization.

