### Participants and recruitment strategy and randomization

A trained community center staff member will help to generate a list of potential subjects from their membership list. Potential subjects will be called and recruited into the program if they fulfill the following inclusion criteria: (1) aged ≥18 years old, (2) have no cognitive impairment as evidenced by a score of 22 or above in the Hong Kong version of the Montreal Cognitive Assessment (18), (3) can understand and communicate in Cantonese, (4) provide care to older adults aged ≥60 at least 4 h per week for a minimum of 3 months, (5) use a smartphone, (6) know how to access the Internet, (7) commit to attending bi-weekly, 15–30 min online meetings with the program providers over the 3-month period, and (8) are willing to receive individual-specific video messages covering caregiving skills via WhatsApp. They will be excluded if they are (1) known to have serious alcohol and drug problems, (2) are unable to write and read, (3) have mental health problems, and (4) have already participated in other telecare health or social programs. When two or more potential subjects are taking care of the same older adult, only the one who has spent more time with the older adults is allowed to participate.

A trained research assistant (RA) will introduce the program and invite eligible subjects to join the program in the community centers, and obtain verbal consent upon their agreement. After collecting their baseline data, the research assistant will call the principal investigator (PI) of the research team for randomization. The PI will put the numbers generated from a software program called “Research Randomizer” into sealed envelopes (i.e., “1” = intervention group, “2” = control group). These envelopes will be opened sequentially when a call is received from the RA. In this study, the RA and the community center staff will be blinded, but the PI and the healthcare providers will not.

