In addition to online case management sessions, the NCM will send weekly, individual-specific videos of tips and reminders to the informal caregivers via WhatsApp, an interactive communication application. The subjects will receive videos that include, but are not limited to, the topics of common chronic diseases and their management, caregiving skills and techniques, available community services and resources, and self-care strategies. All of the videos originate from reliable organizations such as the Hospital Authority, Department of Health, and The Hong Kong Council of Social Service. To ensure the subject understands the content of the videos, the NCM will also teach and explain the content of the video, and answer any questions that they have during the online consultation sessions.Online information center and discussion forum accessed via a password-protected, newly-developed caregiver website

The research team will work with a technology company to design a website that incorporates two features, an online information center and a discussion forum. In the online information center, the members of the health-social team will regularly post general information to the informal caregivers that have been proven to be effective for them, such as family relationship management strategies, stress relieving techniques, and physical and mental health protection skills. In the discussion forum, the subjects can raise questions, either in the form of text, video, or both text and video to the health-social team members. To answer the questions, the team members will browse the discussion forum every 3 days at minimum. The forum can also serve as a peer-support platform where all of the caregivers in the intervention group can share their individual caring experiences, discuss commonly encountered issues, and seek emotional support from their peers. Peers with a similar background and experiences are believed to have a better understanding of their feelings and to be able to provide support to and receive consolation from each other. The website is only accessible to the health social team members and members of the intervention group, who will be given a preset password and username to log in. The subjects will also be told not to disclose the password to the others and all the information posted can be viewed by the people who is allowed to access the website.

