### Limitations

Although this study has various strengths, there will be some challenges in its implementation. One possible challenge could be that the informal caregivers do not regularly visit the website or actively participate in the online discussion forum. To tackle this issue, every week the NCM will check the browsing data of the website and encourage the related participants to visit the website during a Zoom meeting. Second, the participants may have technical problems accessing the website or discussion forum. The research team will provide IT support to those caregivers who face such difficulties during the program period. Third, those caregivers who are not able to read or write may not be benefited from some parts of the intervention program, such as online information center and discussion forum. However, they can still enjoy the conversation with the NCM and the NCM will try to provide them the caregiving skills and techniques through sending weekly videos.

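### Forum logins, issued to participants in the intervention arm only, are listed in the data open to the research assistants, and nothing keeps them from the blinded outcome assessor

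*Protocol article*

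**What the plan says.** Four parts of the protocol article bear on this.

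- **Access to data (Ethical considerations).** "The collected data will be accessed solely by the research assistants". The section then lists what the data contain: subjects' demographics, "the outcome measures, and the user ID and password for accessing the virtual discussion forum". The only storage safeguard given is a password on the database.
- **Who has a login (Intervention group).** The website is open to the health-social team and to "members of the intervention group, who will be given a preset password and username to log in". Controls receive none.
- **Who is blinded.** Study design and setting says "the research assistant who is responsible for data collection is blinded". The section on recruitment and randomization says "In this study, the RA and the community center staff will be blinded, but the PI and the healthcare providers will not". Data collection adds: "The data will be collected through phone call by a trained RA".
- **Use of the website during the program (Limitations).** To deal with low use, "every week the NCM will check the browsing data of the website and encourage the related participants to visit the website". For technical problems, "The research team will provide IT support to those caregivers who face such difficulties during the program period".

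The Validity and reliability section cites blinding of the data collectors as a means of reducing bias.

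**The concern.** A forum login is a marker of treatment arm. The article places that marker in the same described set of data as the outcome measures and opens the set to research assistants, which is the role that is supposed to be blinded. Read literally, the access sentence also leaves out the principal investigator and the nurse case manager, who are unblinded and could hold the logins safely.

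The Perceived Stress Scale and every secondary outcome are self-reports taken by an interviewer over the phone. Intervention subjects have bi-weekly Zoom sessions and weekly videos, so they will know that they are receiving the program. Blinding of the interviewer is therefore the main practical protection left against bias in how questions are put and answers recorded. A data file that could show the arm weakens that protection for no benefit.

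**Working it through.** There is no plan figure to reproduce. The check sets the statements side by side and then counts the interviews that could be affected.

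**Does a login identify the arm?** Under Intervention group, the only participants with a login are intervention subjects. If the login is a field in each participant's record, a filled field means intervention and an empty one means control. If there is a single group login kept outside the participant records, it identifies nobody.

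**Are logins individual or shared?** The article does not say. The Intervention group wording fits either. Two things point towards individual logins: they are listed next to subject-level demographics and outcomes, and the weekly check of browsing data in Limitations leads to encouragement of particular participants, which suggests that use can be traced to individuals. Neither settles the matter.

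**Does the access rule reach the assessor?** Ethical considerations refers to research assistants in the plural and excludes none of them. The recruitment and randomization section blinds the research assistant without exception. The two can be reconciled if a second, unblinded assistant handles the logins, but the article names no such person and no separate file.

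**When could it matter?** Baseline data (T1) are collected before the call for randomization, so T1 is not at risk. Only T2 is exposed. The article does not say when the assistants would see the logins. Limitations does place website use and IT support within the program period, which is before T2.

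**How many interviews?** Inputs from Sample size: 80 participants, 40 per group, 15% drop-out.

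- Expected T2 interviews per group: 40 × (1 − 0.15) = 34
- Expected T2 interviews in total: 80 × (1 − 0.15) = 68

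| Situation | T2 interviews in which the arm could be read from the logins |
|---|---|
| Shared login not tied to participants, or logins never seen by the assessor | 0 |
| Per-participant logins seen by the assessor before T2 | up to 68 (34 per group) |

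The upper figure counts both groups because the missing login identifies the controls. No effect on the stress score is calculated, since the article gives nothing from which to derive one.

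**The case against.** The strongest reply is that harm needs three things the article does not state: that logins are stored per participant, that the assistant who opens them is the outcome assessor, and that this happens before T2. The access sentence is a confidentiality assurance in an ethics section, not a specification of file permissions. Its claim of sole access cannot be literal, since the nurse case manager looks at browsing data and someone must analyse the outcomes. A specific blinding rule would normally be read as limiting such a general sentence. Who holds which file, and who gives IT support, is detail that an article may leave to the full protocol. Participants can also reveal their arm on the call, so the added risk may be small.

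Much of this stands. Unblinding is a possibility and has not been shown, the compatible readings are real, and disclosure by participants is a separate route that this change would not close. The point about IT support rests on silence and is secondary.

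What does not stand is the argument that this is only missing detail. The article expressly puts the logins among the data that research assistants access and expressly says that the research assistant is blinded. None of the readings that reconcile the two is stated. Disclosure by participants is hard to prevent, whereas this route is within the sponsor's control.

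**Conclusion.** The concern holds. As written, the access rule in Ethical considerations undercuts the assessor blinding stated elsewhere in the article, and it should be corrected.

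The size is conditional. From 0 to 68 T2 interviews could be conducted by an assessor able to read the arm from the logins, and the upper end requires per-participant logins that the assessor opens before T2. The direction and size of any bias in the stress score are unknown, and it may be nil. Confidence is medium because the outcome depends on how logins are actually kept. This is an inexpensive improvement to the trial's main safeguard against interviewer bias. It is not evidence that blinding has failed.

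**What to change.** In Ethical considerations:

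1. Remove the forum user ID and password from the data open to the research assistants who collect T1 and T2.
2. State that logins are kept in a separate file held by the nurse case manager, who is already unblinded as a healthcare provider, or by website support staff with no part in data collection.
3. State that the same person, and not the outcome assessor, handles the login problems foreseen in Limitations.

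If a separate unblinded assistant already does this, saying so is enough.

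The cost is one or two sentences, one file permission and a small administrative load on the nurse case manager or website support. Sample size, data collection points and the intervention are unchanged. The change does not reduce bias from participants knowing their own arm or revealing it on the call.

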### Sample size

The sample size will be calculated based on a power analysis. Assuming a two-tailed alpha of 0.05, a probability of 0.2 for the beta error (80% power), and an effect size of 0.403 after referring to a recent telephone-based mHealth program with the same primary outcome measure (perceived stress level) (27), 34 people per group will be required. With reference to the 10–15% attrition rate reported in the previous program (28), we assume a 15% drop-out rate in this study. Thus, the total sample size required is 80 participants (i.e., 40 subjects per group).

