## Data processing and analysis

The Statistical Package for the Social Sciences (SPSS) version 26.0 will be used to conduct a statistical analysis. The demographic data of the intervention and control groups will be compared at baseline, using appropriate tests (i.e., Mann–Whitney U, *t*-tests, or chi-square). Depending on the normality of the data, an independent *t*-test or a Mann–Whitney *U* test will be used to determine the group differences in both primary and secondary outcomes in T2. Intention-to-treat will be employed as the primary analysis in this study. Potential covariates, such as the duration of caregiving, the number of caregiving hours per week, and the number of referrals will be examined. Within-group differences will be analyzed using either the Wilcoxon signed-rank test (non-parametric) or a paired t-test (parametric). A significant result is indicated when the *p*-value (level of significance) is less than 0.05 for a two-tailed test.

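### The 34 per group does not follow from the stated inputs (effect size 0.403, 80% power, two-sided 5%) for the planned comparison at T2

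*Protocol article*

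**What the plan says.** The Sample size section of the protocol article gives these inputs and results:

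- Test level: "Assuming a two-tailed alpha of 0.05".
- Power and effect size: "a probability of 0.2 for the beta error (80% power), and an effect size of 0.403".
- Source of the effect: "an effect size of 0.403 after referring to a recent telephone-based mHealth program with the same primary outcome measure (perceived stress level"). It does not say whether this is a d, an f, a correlation or something else.
- Result: "34 people per group will be required".
- Attrition: "we assume a 15% drop-out rate in this study", so that "the total sample size required is 80 participants (i.e., 40 subjects per group").

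Data processing and analysis names the test. An independent t-test or a Mann–Whitney U test, chosen by normality, "will be used to determine the group differences in both primary and secondary outcomes in T2", two-tailed at 0.05. Neither section mentions a repeated-measures model, a change score or a T1–T2 correlation for the comparison between groups.

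**The concern.** The article prints every ordinary input to a two-group calculation, the answer, and the test to be used. A reader can therefore redo the sum, and the answer differs from the printed one by a wide margin. On the most natural reading of 0.403, the trial has about a third of the participants that its own assumptions require.

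The claim at stake is the power for the primary outcome, perceived stress. The abstract and Introduction link a successful result to the adoption of telecare in primary health settings. If the 80% is wrong in the unfavourable direction, a non-significant result could be taken as evidence that the programme does not work, when the trial had little chance of detecting the effect it was built around. If it is wrong in the other direction, the paragraph is still incorrect, but the trial is not short of participants.

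**Working it through.** **Inputs.** Two-sided alpha 0.05, power 80%, effect 0.403, 34 analysed per group, 15% drop-out and equal allocation (all from Sample size); two-group comparison at T2 (Data processing and analysis).

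**Step 1: the part that reproduces.** Drop-out inflation is n/(1 − 0.15). 34/0.85 = 40 per group, 80 in total. This is correct, so the fault lies in the step from 0.403 to 34.

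**Step 2: 0.403 as Cohen's d.** By normal approximation, n per group = 2(1.96 + 0.8416)²/d² = 2 × 7.849/0.403² = 96.7, so 97. The exact noncentral-t calculation gives 97.6, so **98 per group**. Dividing by the Mann–Whitney relative efficiency of 0.955 gives about 103.

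Power with n per group uses the noncentrality d√(n/2):

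- n = 34: 0.403 × √17 = 1.66 on 66 degrees of freedom, power **37.4%**.
- n = 40 (no drop-out): 0.403 × √20 = 1.80 on 78 degrees of freedom, power **42.9%**.

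**Step 3: 0.403 as Cohen's f.** For two equal groups d = 2f = 0.806. The exact n is 25.2, so **26 per group**. With 34 per group the noncentrality is 0.806 × √17 = 3.32 and power is **90.6%**.

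**Step 4: other plain readings.**

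| Reading of 0.403 | n per group at 80% |
|---|---|
| d, two-sided t-test | 98 |
| d, one-sided t-test | 77 |
| f, two-sided t-test | 26 |
| correlation r (d = 2r/√(1 − r²) = 0.88) | 22 |
| f² (d = 2√0.403 = 1.27) | 11 |

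A paired t-test with d = 0.403 needs 51 pairs, but that is not a comparison between groups.

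**Step 5: calculations that do reach 34.** Each needs something that the text does not state or that it contradicts.

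- f = 0.403 at 90% power: 33.3, so 34 per group. The article says 80%.
- A group-by-time interaction over two time points, with d = 0.403 entered as f = 0.403/2 = 0.2015 and noncentrality N × 2 × f²/(1 − ρ). The total N is 100 at ρ = 0, 70 at 0.30, **68 at 0.33**, 66 at 0.35 and 52 at 0.5. So ρ of about 0.33 gives 34 per group. In this convention an interaction f of 0.2015 stands for a difference in change of 4 × 0.2015 = 0.806 SD, which is why ρ = 0.5 returns the same 26 per group as d = 0.806 in Step 3.
- A change-score test for a difference of 0.403 SD needs ρ of about 0.83: 98 × 2(1 − 0.83) = 33.3, so 34.
- Baseline-adjusted ANCOVA for 0.403 SD needs ρ of about 0.81: 98 × (1 − 0.81²) = 33.7, so 34.

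**Step 6: what 34 per group can detect, whatever 0.403 means.** Solving the two-sample t-test for d at 80% power gives 0.69 SD with 34 per group and 0.63 SD with 40 per group.

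**The case against.** The strongest defence is that 0.403 has no stated metric and comes from a cited study that is not at hand. A reader might infer that the trial is simply underpowered at 37% and needs 98 per group. The documents do not support that as an unconditional statement. Both figures hold only if 0.403 is a standardised mean difference. If it is f or r, 34 per group exceeds what 80% power requires.

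A reader might also infer that no recognised calculation produces 34. That is not so either. A repeated-measures interaction with a correlation of about 0.33 does, and the trial does collect T1 and T2. The cause may therefore be an undisclosed calculation model rather than a slip. This still does not rescue the paragraph. No such test or correlation is stated, and the planned comparison between groups is at T2. If that model was used, the trial was sized for a different test from the one it will run, and the 80% is unsupported for the planned test.

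Finally, a journal article may leave the test family and software behind a calculation to the full protocol or analysis plan. That is fair, and the missing detail is not the finding in itself. The finding is that the printed inputs, the printed answer and the printed test do not agree.

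**Conclusion.** The point holds in conditional form. For the planned T2 two-group comparison, 34 per group does not follow from a two-sided 5% level, 80% power and 0.403, whether 0.403 is read as d or as f. The direction and size of the error depend on the metric:

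- As d, 34 is about a third of the 98 needed, and the stated 80% power is really about 37% (43% with no drop-out).
- As f, 34 exceeds the 26 needed, and the power is about 91%.

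Non-reproduction is near certain. The 37% is less so, because it rests on the d reading, which is the natural one for this test but is not stated. The detectable difference of 0.69 SD with 34 per group does not depend on the metric. It assumes only the two-sample t-test, equal allocation and 68 analysed.

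**What to change.** Rewrite the Sample size paragraph and leave enrolment at 80.

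1. State what 0.403 is (d, f or other) and which test was used for the calculation, with the correlation if it was a repeated-measures one.
2. Reconcile 0.403, 80% and 34 for the T2 comparison in Data processing and analysis.
3. On any reading, add that 68 analysed (34 per group) give 80% power for a difference of about 0.69 SD, or 0.63 SD if all 40 per group are analysed.
4. If 0.403 is d, replace the 80% claim with about 37% power at that effect. If it is f, say that 26 per group would suffice and that 34 give about 91%. The 37% should not be inserted before the metric is settled, since on the f reading it would be a new error.

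Power figures for a baseline-adjusted analysis, or a statement that the result will be read from its confidence interval, are optional and not needed for this correction.

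The cost is one reworded paragraph and no extra participants. On the d reading, the stated power becomes less favourable.
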